#### Baseline assessment.

Between enrollment and the baseline laboratory visit, participants will complete a series of online questionnaires assessing demographics, medical and neurological history, sexual behavior history, and Adverse Childhood Experiences (ACES). At the baseline visit, participants will undergo various assessments, including testing day questionnaires to gauge various contextual information (menstrual cycle, exercise), capillary blood sampling to test blood fatty acid components, urinalysis to verify pregnancy status, blood sampling for biomarker analysis, MRI, cognitive testing, oculomotor assessments, retinal imaging, and mental health questionnaires. Baseline assessments are designed to characterize neurological health prior to acute or longitudinal exposure assessment and to allow examination of baseline group differences between participants with frequent sexual strangulation exposure and non-strangulation controls. The baseline visit will end with setting up a MyCap account within Research Electronic Data Capture (REDCap) for participants for acute visit purposes. Participants in both the strangulation group and control group will participate in the acute aim (aim 2), but control participants who are not sexually active will not be participating in the acute aim.

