Inclusion and exclusion criteria are summarized in Table 2. For the strangulation group, inclusion requires self-report of being strangled during sex at least four times in the month prior to enrollment, which will be verified during a screening interview. Control participants must report no lifetime history of sexual strangulation. Exclusion criteria are limited to conditions necessary for participant safety or study feasibility and include head or neck injury in the past 6 months including concussions, current diagnosis of psychosis, schizophrenia, and seizure disorder, currently taking anti-psychotic medicine, history of brain aneurysm or brain tumor, and current pregnancy. Common psychiatric conditions prevalent in young adults, including depression, anxiety disorders, bipolar disorder, and attention-deficit/hyperactivity disorder (ADHD), will not be excluded and will be assessed and accounted for analytically. Additionally, participants with implanted metal/electro/magnetic devices will not undergo MRI data collection, but they will complete all other assessments; thus, not excluded from the study.

**Table 2 pone.0344672.t002:** Inclusion and exclusion criteria.

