**Inclusion Criteria**
• 18–26 years of age
• Being strangled during sex, on average, three times in the past month (strangulation group)
• Age-matched participants with no lifetime experience of being strangled during sex (control group).

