#### Acute assessment following sexual activity.

Participants eligible for the acute aim will be monitored following baseline assessment using brief daily electronic surveys to determine the occurrence of sexual activity and the presence or absence of strangulation. For participants in the strangulation group, an acute laboratory visit will be scheduled within approximately 24 hours following a sexual event involving strangulation. For control participants, an acute visit will be scheduled within approximately 24 hours following a sexual event without strangulation. Participants who do not engage in sexual activity during the monitoring period will remain eligible for longitudinal follow-up but may not contribute to acute analyses. The acute visit will replicate key components of the baseline assessment, including blood collection, neuroimaging, cognitive testing, oculomotor and retinal assessments, and mental health questionnaires. These data will be used to characterize short-term neurological responses associated with sexual strangulation relative to baseline and control conditions.

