#### Psychiatric and mental health questionnaires.

The following questionnaires will be used to gauge symptoms related to various psychiatric and mental health conditions, including Patient Health Questionnaire-9 (PHQ-9) for depression, Generalized Anxiety Disorder-7 (GAD-7) for anxiety, Perceived Stress Scale (PSS) for perceived stress, adult ADHD self-report scale (ASRS) for ADHD-related symptoms, Multidimensional Personality Questionnaire (MPQ) for personality traits, Extended–Hurt, Insulted, Threaten, Scream (E-HITS) for history of domestic/intimate partner violence with an additional question regarding strangulation experience, Penn State Electronic Cigarette Dependence Index (PS-ECDI) for e-cigarette use, Pittsburgh Sleep Quality Index (PSQI) for sleep, Migraine Disability Assessment (MIDAS) for migraine, Life Events Checklist-5 (LEC-5) to screen for lifetime traumatic events, and PTSD Checklist for DSM-5 (PCL-5) to assesses symptoms of PTSD.

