### Statistical analyses

#### Baseline group analysis.

To test whether neurological outcomes differ at baseline between the strangulation and control groups, we will use multivariable regression models with each baseline neurological outcome as the dependent variable and group (strangulation vs control) as the primary independent variable. For continuous outcomes (e.g., biomarker concentrations, imaging metrics, cognitive scores, NPC distance, OCT measures), we will use linear regression (or generalized linear models with appropriate functions if distributional assumptions are not met). For binary outcomes (e.g., presence/absence of symptoms or threshold-defined impairment), we will use logistic regression. Models will adjust for prespecified baseline covariates that are clinically relevant and/or imbalanced between groups, including age, BMI, prior concussion history, and baseline mental health symptoms. Because baseline neural health may be influenced by contextual factors, we will additionally consider time since last sexual event, substance use, sleep, and ovarian hormone levels/menstrual cycle phase as covariates when relevant to specific outcomes. For imaging outcomes, scanner-related and acquisition covariates (e.g., motion indices) will be included as standard quality-control adjustments. We will control for multiple comparisons using a false discovery rate (FDR) approach within each modality (biomarkers, imaging, ocular/retinal, cognition, mental health). As a complementary approach that leverages correlation among outcomes, we will conduct multivariate testing within domains (e.g., principal-component-based composite scores) to evaluate whether a domain shows an overall baseline difference by group prior to interpreting individual endpoints. Where appropriate, we also may consider exploratory mediation and explanatory models to help explain baseline group differences. We will use mediation analyses to estimate indirect effects while adjusting for confounders.

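### Controls need not be sexually active, so the Aim 1 group contrast, and partly the Aim 3 one, mixes strangulation with sexual activity; no covariate list names sexual activity level, partner violence, childhood adversity or lifetime trauma

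*Protocol article*

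**What the plan says.** **Who is compared.** Under Participants, for the strangulation group, "inclusion requires self-report of being strangled during sex at least four times in the month prior to enrollment". Table 2 gives three times on average. The two figures need reconciling, but either one means that the whole group is frequently sexually active. For controls, "Control participants must report no lifetime history of sexual strangulation", and Table 2 adds only age: "Age-matched participants with no lifetime experience of being strangled during sex (control group". Nothing requires a control to be sexually active.

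**Who is left out, and where.** Baseline assessment: "control participants who are not sexually active will not be participating in the acute aim". Acute assessment following sexual activity: "Participants who do not engage in sexual activity during the monitoring period will remain eligible for longitudinal follow-up". The Longitudinal follow-up section takes in every participant.

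**What is adjusted for.** In Aim 1, the covariates are those judged clinically relevant or found imbalanced. Age, BMI, concussion history and baseline mental health symptoms are given as members of that set. Beyond these, "we will additionally consider time since last sexual event, substance use, sleep, and ovarian hormone levels/menstrual cycle phase as covariates", but only where relevant to the outcome. In Aim 3, the list is age, concussion history, mental health diagnosis and other time-varying factors, with mental health symptoms and substance use as examples.

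**What is collected.** The baseline questionnaires cover "sexual behavior history, and Adverse Childhood Experiences (ACES". E-HITS is used "for history of domestic/intimate partner violence with an additional question regarding strangulation experience". LEC-5 screens for lifetime trauma, and ASSIST is given at screening.

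**The concern.** Aim 2 compares strangulation sex with sex without strangulation, which is a sound contrast. Aims 1 and 3 do not keep it. There, a difference between groups could come from strangulation, from being sexually active, or from violence and adversity that differ between the groups.

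The protocol itself treats sexual activity as something that can move the outcomes. The Introduction refers to positive effects of sex on mental health, which is a primary outcome. Participants must refrain from sex on the day of the baseline visit. The Introduction also names intimate partner violence as a setting in which brief hypoxia disrupts neural integrity. Head or neck injury is an exclusion only within the past 6 months, so older violence-related injury can be present in either group.

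The Introduction faults earlier work for its limited ability to separate pre-existing differences from effects of strangulation. That separation is at stake here.

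**Working it through.** **1. The plan's own figure.** Sample size states more than 80% power for the longitudinal contrasts with 100 females per group, d = 0.50, alpha 0.01 and 20% dropout or switching. For a simple two-sided comparison with SD = 1, power = Φ(d/SE − 2.576), where SE = √(1/n₁ + 1/n₂).
- 100 vs 100: SE = √0.02 = 0.1414; 0.50/0.1414 = 3.536; Φ(0.960) = 83%.
- 80 vs 80, after 20% loss: SE = √0.025 = 0.1581; 3.162; Φ(0.587) = 72%.

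The repeated-measures correlation is not given, so the stated design cannot be reproduced exactly, and repeated measures could raise these values. The present point does not depend on them.

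**2. Aim 1: what the group term estimates.** Let f be the share of inactive controls and δ the effect of sexual activity in SD units. With no strangulation effect at all, the expected group difference is b = f × δ. Neither input is in the documents, so both are assumed: f from 10% to 50%, δ from 0.2 to 0.5 SD.
- Lowest: 0.10 × 0.2 = 0.02 SD.
- Highest: 0.50 × 0.5 = 0.25 SD.

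With 100 per group, SE = √(1/100 + (1 + f(1−f)δ²)/100). The chance of rejecting at a nominal two-sided 0.01 is Φ(b/SE − 2.576) + Φ(−b/SE − 2.576).

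| f | δ (SD) | b (SD) | Rejection rate |
|---|---|---|---|
| 0.10 | 0.2 | 0.02 | 0.011 |
| 0.20 | 0.5 | 0.10 | 0.031 |
| 0.30 | 0.5 | 0.15 | 0.063 |
| 0.50 | 0.5 | 0.25 | 0.20 |

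An unadjusted imbalance in violence or adversity works the same way. A difference of 10–30 percentage points in prevalence (assumed) with an effect of 0.2–0.5 SD (assumed) gives 0.02–0.15 SD.

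**3. Aim 3: what the interaction estimates.** The group × time contrast at visit t is the group difference at t minus that at baseline. A level bias b is present in both terms, and b − b = 0. Bias remains only if the effect of sexual activity, violence or adversity changes over follow-up. The Aim 1 figures therefore must not be carried over to Aim 3.

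**4. Do the named covariates remove it?**
- Recency of the last sexual event is only conditional in Aim 1, is not in the Aim 3 list, and has no value for a control who has never had sex. It also measures recency, not level of activity.
- No list names E-HITS, ACES or LEC-5. The Aim 1 imbalance rule could admit them but does not ensure it.
- Childhood adversity is fixed, so it cannot enter Aim 3 as a time-varying factor. Entered there as a main effect alone, it would barely change a group × time estimate.
- Hypothesis 1b would explore history factors as mediators. Childhood adversity comes before exposure, so it belongs among the confounders.

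**The case against.** The other side has real force on several counts.

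- **A reader might infer that no model adjusts for collected confounders.** That is not supported. Aim 1's rule is open to any imbalanced covariate; concussion history and mental health are adjusted for; substance use is considered in Aim 1 and named in Aim 3. Hypothesis 1b, Exploratory Aim 6 and the mediation analyses also look at behavioral and history factors, though only as exploration.
- **A reader might infer that all of Aim 3 is affected.** It is not. The exposure-response models run within the strangulation group, so inactive controls cannot distort them. Confounding by violence or adversity can.
- **A reader might infer that the bias inflates the strangulation effect by some share of d = 0.50.** The sign is unknown. If sex improves mental health, inactive controls would look worse, and the group difference on those outcomes would shrink.
- **A reader might infer that the E-HITS addition records non-sexual strangulation, or that controls without a last sexual event must drop out of the models.** The text says only strangulation experience, and categorical coding could keep such controls in.
- **A full covariate list may stand in an analysis plan that is not shown.** True. But control eligibility is a protocol decision, and the article does state its covariates for each aim. As stated, they leave this confounding in place.
- **The Discussion accepts that the design precludes causal inference.** That limits the claims but does not excuse leaving out confounders already measured.

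Making sexually active controls the primary comparator, or forcing past-month sexual frequency into every model, is debatable. The first costs power. The second is tied to entry into the exposed group and would give poor overlap.

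**Conclusion.** The concern holds in a bounded form. The Aim 1 group contrast mixes strangulation with sexual activity. The Aim 3 group × time contrast does so only to the extent that effects change over time. No model names sexual activity level, partner violence, childhood adversity or lifetime trauma as a covariate, although the protocol collects data on all of them.

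The documents support no estimate of size or direction. The range of 0.02–0.25 SD rests wholly on the assumed share of inactive controls and the assumed effect of sexual activity, and it applies to Aim 1 only. Near its lower end the rejection rate hardly moves from 0.01; at its upper end it reaches about 0.20. The 0.01 level is the one used for sample size; the analyses themselves control the false discovery rate within modality. The change should be made because it is cheap and the data are already being collected, not because a large bias has been shown.

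**What to change.** 1. **Aim 1 group contrast.** Put ACES, the E-HITS partner-violence items, LEC-5 and baseline ASSIST into the fixed adjustment set, whether or not they prove imbalanced. Keep the E-HITS strangulation question separate, so that exposure is not adjusted away.
2. **Aim 3 group × time model.** Enter the same covariates with covariate × time terms.
3. **Both group contrasts.** Prespecify a key sensitivity analysis restricted to sexually active controls, defined from the sexual behavior history already collected.
4. **Recruitment.** Where possible, favour sexually active controls when inviting from the campus survey.

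**Cost.** The adjustment uses some degrees of freedom, more in Aim 3 because time is categorical with six levels. The restricted analysis loses precision. With 20% of controls inactive and not replaced (100 vs 80), SE = √(1/100 + 1/80) = 0.15, 0.50/0.15 = 3.333, and power is Φ(0.758) = 78%, against 83% with all controls (two-sided, d = 0.50, alpha 0.01, before losses). At 10%, 30% and 50% inactive it is 81%, 74% and 62%. The invitation preference limits this loss. Because the restricted analysis is a sensitivity analysis, the primary contrast keeps every control.

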#### Acute assessment following sexual activity.

Participants eligible for the acute aim will be monitored following baseline assessment using brief daily electronic surveys to determine the occurrence of sexual activity and the presence or absence of strangulation. For participants in the strangulation group, an acute laboratory visit will be scheduled within approximately 24 hours following a sexual event involving strangulation. For control participants, an acute visit will be scheduled within approximately 24 hours following a sexual event without strangulation. Participants who do not engage in sexual activity during the monitoring period will remain eligible for longitudinal follow-up but may not contribute to acute analyses. The acute visit will replicate key components of the baseline assessment, including blood collection, neuroimaging, cognitive testing, oculomotor and retinal assessments, and mental health questionnaires. These data will be used to characterize short-term neurological responses associated with sexual strangulation relative to baseline and control conditions.

#### Longitudinal follow-up.

All participants will enter a longitudinal follow-up phase consisting of laboratory visits every six months for up to 30 months following baseline assessment. Each follow-up visit will include repeat multimodal neurological assessments identical to baseline measures, allowing evaluation of changes in neural cellular, physiological, and functional integrity over time. Longitudinal assessments are designed to capture cumulative exposure effects and temporal trajectories of neurological health associated with sexual strangulation. Participants who change sexual behavior during the study (e.g., controls initiating sexual strangulation or strangulation participants discontinuing the behavior) will continue follow-up when feasible. Data collected prior to behavioral change will contribute to primary analyses, while post-change data will be used in exploratory analyses to examine within-individual changes.

#### Semi-structured interviews.

Semi-structured interviews will be conducted at baseline (within 1 week from the baseline neurological assessments), following acute laboratory visits (within 72 hours), and after each longitudinal follow-up visit (within 1 week from the baseline neurological assessments). Interviews will assess participants’ experiences with sexual strangulation, including frequency, duration, methods, perceived consent, contextual factors, associated symptoms, and changes in behavior over time. These interviews will provide behavioral and contextual data to complement neurobiological findings and to inform interpretation of neurological outcomes.

### Measurements

#### Blood fatty acid composition.

At baseline and all follow-up timepoints, a capillary blood sample from a fingertip will be collected and sent to OmegaQuant Analytics for blood fatty acids composition analysis.

#### Psychiatric and mental health questionnaires.

The following questionnaires will be used to gauge symptoms related to various psychiatric and mental health conditions, including Patient Health Questionnaire-9 (PHQ-9) for depression, Generalized Anxiety Disorder-7 (GAD-7) for anxiety, Perceived Stress Scale (PSS) for perceived stress, adult ADHD self-report scale (ASRS) for ADHD-related symptoms, Multidimensional Personality Questionnaire (MPQ) for personality traits, Extended–Hurt, Insulted, Threaten, Scream (E-HITS) for history of domestic/intimate partner violence with an additional question regarding strangulation experience, Penn State Electronic Cigarette Dependence Index (PS-ECDI) for e-cigarette use, Pittsburgh Sleep Quality Index (PSQI) for sleep, Migraine Disability Assessment (MIDAS) for migraine, Life Events Checklist-5 (LEC-5) to screen for lifetime traumatic events, and PTSD Checklist for DSM-5 (PCL-5) to assesses symptoms of PTSD.

#### Blood biomarker assessment.

Capillary blood sampling using the Tasso blood collection device will be performed each test session. A trained phlebotomist will thoroughly clean the area with an alcohol swab and collect two sets of 400 μL of capillary blood sample using the Tasso device. Plasma levels of NF-L, Tau, UCH-L1, GFAP, p-tau 181, and p-tau 217 will be assessed by Quanterix’s Simoa SR-X assays. Various cytokines and chemokine markers, including S100B, IL-1b,1a,2,6,8,10,17; CCL2,3,5,11; and VCAM, PCAM, angiopoietin, and neuregulin, will be assessed by custom Luminex panels.

#### Neuroimaging assessment.

Neuroimaging assessments will take place in the Indiana University’s Imaging Research Facility (IRF), which houses a research-dedicated 3T Siemens Prisma MRI scanner equipped with a 64-channel head/neck coil.

High-resolution anatomical images (T1), which will be used for morphometry analyses, will be acquired using 3D MPRAGE pulse sequence: TR/TE = 2400/2.3ms, TI = 1060ms, flip angle = 8, field-of-view = 256 mm, matrix = 320x320, bandwidth = 160 Hz/pixel, iPAT = 2, resulting in 0.8 mm isotropic resolution. Both resting state fMRI (rs-fMRI) and task-based fMRI data will be collected using an SMS single-shot EPI sequence: FOV = 216 mm, TR/TE = 800/30 ms, flip angle = 52°, matrix = 90 × 90, resolution = 2.4 mm isotropic, and multiband acceleration factor = 6, with 100 volumes for rs-fMRI and 240 volumes for task-based fMRI. The rs-fMRI data will be acquired while the participant relaxes with eyes open and passively views a crosshair for 12 minutes. For task-based fMRI, the BART task [34], which has two, 8-min blocks, will be administered. As participants continue to inflate a balloon for greater reward, the probability of an explosion increases to mimic real-world risk-reward decision making. For each trial, the screen will display the image of a purple balloon above a small green rectangle, which indicates that she/he needs to make a decision (inflate or win). Participants will accumulate their win/wager throughout the two, 8-min block, experiments. Potential regions of interest (ROI) include the dorsal anterior cingulate cortex (dACC), nucleus accumbens (NAc), and insula due to their involvement in reward and decision-making processes [35]. Our DTI protocol is adapted from the Adolescent Brain Cognitive Development study [36], which is optimized for NODDI analysis. Two consecutive DTI sessions with opposite phase encoding directions will be performed with a simultaneous multi-slice (SMS) single-shot spin-echo echo-planar imaging (EPI) pulse sequence (TE = 89.4ms; TR = 3590s, 1.5 mm isotropic resolution). Each session has 80 images with different diffusion weightings and gradient directions (7 b = 0 s/mm2, 6 directions with b = 500 s/mm2, 15 directions with b = 1000 s/mm2, 15 directions with b = 2000 s/mm2, and 60 directions b = 2500 s/mm2). The total scan time is 10 minutes. Quantitative Susceptibility Mapping (QSM) will be collected using a three-dimensional flow-compensated multiecho gradient-echo sequence with a repetition time of 45 msec, a total of five echoes (time of the first echo, 13 msec) with echo spacing of 6 msec, flip angle of 20°, field of view of 24 × 24 cm, matrix of 512 × 256, and 88 sections acquired with 1.5-mm thickness.

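### The fMRI volume counts do not fit the stated run times, and the diffusion image list does not add up to the stated count, for imaging outcomes classed as primary

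*Protocol article*

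**What the plan says.** All the figures come from the Neuroimaging assessment section of the protocol article.

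- **Shared fMRI sequence.** Resting-state and task fMRI use the same EPI sequence: "TR/TE = 800/30 ms, flip angle = 52" degrees, "with 100 volumes for rs-fMRI and 240 volumes for task-based fMRI".
- **Resting run.** The participant "passively views a crosshair for 12 minutes".
- **Task run.** The BART is a task "which has two, 8-min blocks, will be administered". The 8-minute block length appears a second time in the same section. The text does not say whether the 240 volumes are per block or for both blocks.
- **Diffusion.** "Each session has 80 images with different diffusion weightings and gradient directions". The list that follows is "7 b = 0 s/mm2, 6 directions with b = 500 s/mm2, 15 directions with b = 1000 s/mm2", then "15 directions with b = 2000 s/mm2, and 60 directions b = 2500 s/mm2". Two sessions with opposite phase encoding are planned, the total scan time is given as 10 minutes, and the TR is printed as 3590 with the unit in seconds.

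Table 1 labels both fMRI (resting connectivity and BART activation) and structural neuroimaging (which includes DTI and NODDI) as primary outcomes.

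**The concern.** Volumes, TR and run time are tied by one multiplication, and here they disagree by a wide margin. The diffusion image count also disagrees with its own breakdown in the same sentence.

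Run length sets how much data stands behind each connectivity or activation estimate, and the shell scheme sets what feeds the NODDI model. As printed, a reader cannot tell whether resting connectivity rests on 80 seconds or 12 minutes of data, how much of the BART is imaged, or which diffusion scheme is used. Imaging is repeated at the acute and six-monthly visits, and a run acquired too short cannot be recovered afterwards.

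**Working it through.** **Inputs** (Neuroimaging assessment section): fMRI TR 0.8 s; 100 resting and 240 task volumes; 12 min of rest; two 8-min BART blocks; diffusion 80 images per session, list 7, 6, 15, 15, 60; two sessions; 10 min in total; diffusion TR read as 3590 ms = 3.59 s (assumption, see step 5).

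**Formulas.** Run time = volumes × TR. Volumes needed = run time / TR. Image count = sum of the listed shells.

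**1. Resting state**
- Printed count: 100 × 0.8 s = 80 s (1.33 min).
- Needed for 12 min: 720 / 0.8 = 900 volumes.
- Coverage: 100 / 900 = 11%, a ninefold gap.

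**2. BART**
- Printed count: 240 × 0.8 s = 192 s (3.2 min).
- Needed per block: 480 / 0.8 = 600 volumes. Needed for both: 960 / 0.8 = 1200.
- Coverage if 240 is per block: 240 / 600 = 40% (two blocks give 384 s of 960 s).
- Coverage if 240 is the total: 240 / 1200 = 20%.

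**3. Could a misprinted TR explain it?**
- Rest: 720 / 100 = 7.2 s.
- BART: 480 / 240 = 2.0 s per block, or 960 / 240 = 4.0 s in total.
- The runs share one sequence, and no single TR fits both. Correcting the TR alone cannot reconcile the text.

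**4. Diffusion image count**
- 7 + 6 + 15 + 15 + 60 = 103 images, against 80 stated: 23 more.
- Without the 7 b=0 images: 6 + 15 + 15 + 60 = 96 directions, also not 80.
- No subset of the five listed numbers sums to 80.

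**5. Diffusion scan time**
- Taken literally, 80 images at 3590 s last about 80 hours, so the unit is a slip.
- With 3.59 s and 80 images: 2 × 80 × 3.59 / 60 = 9.6 min, which reproduces the stated 10 minutes.
- With 3.59 s and 103 images: 2 × 103 × 3.59 / 60 = 12.3 min, which does not.

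**The case against.** The best defence is that these are reporting slips. The article states the 12-minute rest outright and the 8-minute block twice. A count of 240 at 2.0 s is exactly 8 minutes, so it could have been carried over from another sequence, though the article does not say so. The diffusion unit error could mislead nobody. Nothing here touches the hypotheses, sample size, models or multiplicity control. All of this is fair, and it limits the consequence. It does not remove the contradiction: the figures are stated, they conflict, and no other section resolves them. Nor is this a matter of an article condensing a fuller document, since nothing is claimed to be missing.

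A reader might infer that primary imaging data will be lost at every visit for every participant. The article does not support that:

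- Loss requires the printed counts to be the programmed ones, which is nowhere stated.
- Participants with implanted devices are not scanned (Participants section).
- Controls who are not sexually active do not join the acute aim (Baseline assessment), and participants with no sexual activity during monitoring may not contribute to it (Acute assessment).

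A reader might also infer that the durations, or the 103 images, are the correct values. The article does not settle which member of any pair is intended. The 80-image count agrees with the 10-minute time, so the shell list may be the misprint, but that is an inference.

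**Conclusion.** The acquisition parameters are inconsistent as written for outcomes classed as primary, and this should be corrected. At a TR of 800 ms the printed resting count covers 80 s of a stated 12 minutes. The printed task count covers 192 s, against 8 minutes per block. The diffusion list exceeds the stated image count by 23.

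The practical consequence is conditional. If the printed counts are programmed, scanned participants yield 11% of the stated resting duration and 20% to 40% of the BART duration, the range reflecting whether 240 is a total or a per-block count. If the stated durations are run, the fault is confined to the publication, which would then describe an acquisition that cannot be reproduced. The fMRI arithmetic rests only on printed figures; the diffusion timing also assumes that the TR is 3590 ms.

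**What to change.** Compare the section with the scanner protocol export. Recruitment was anticipated to start in late February 2026, so if scanning has begun, check the acquired run lengths as well. Then:

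1. Make sure the programmed volumes cover the whole 12-minute resting run and both 8-minute BART blocks at the TR actually used. At 0.8 s that means 900 volumes and 600 per block. If the TR or a duration is the misprint, restate that instead.
2. Say whether the task volume count is per block or in total.
3. Reconcile the diffusion image count, the shell list and the 10-minute scan time, counting b=0 images separately from directions.
4. Give the diffusion TR in milliseconds.

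The cost is one check against the export and a text correction. If scans have already been acquired with short runs, the sponsor needs to know how many before the imaging analyses are finalised.
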